### Selection of the study population

#### Inclusion criteria

Patients selected from the database will be aged 18 years or over and have a body mass index (BMI) of over 13kg/m^2^. Other inclusion criteria will be an ICU length-of-stay (LOS) of > 48 hours. The rationale behind this inclusion criterion is that the potentially detrimental effects of propofol on survival are not attributable to immediate or acute reactions, but instead require more than 48 hours of therapy to manifest (e.g., in the event of propofol infusion syndrome).^(1,14)^

For patients admitted to the same unit during the same hospital stay, we will only analyze the first ICU admission. Patients readmitted after hospital discharge will be included as separate cases.

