### Confounder variables

The list of confounder variables is presented in table 1. To account for heterogeneity across ICUs, all models will include random effects for each unit.

**Table 1 t1:** List of confounder variables. In addition to these variables, all models will contain a random intensive care unit variable

Variable	Time of recording
Number of days on oral nutrition	Days 0 - 2 post ICU admission
Number of days on parenteral nutrition	Days 0 - 2 post ICU admission
Number of days with protein intake > 1.2g/kg day	Days 0 - 2 post ICU admission
Year of therapy	Admission date
APACHE II score	ICU admission
Main admission diagnosis*	ICU admission
Admission category (surgical elective/emergency, medical)	ICU admission
Age	ICU admission
Sex	ICU admission
BMI	Pre-ICU admission
Baseline number of days under MV†	Days 0 - 2 post ICU admission
Number of days under MV before state transition‡	Days 0 - 11 post ICU admission

ICU – intensive care unit; APACHE - Acute Physiology and Chronic Health Evaluation; BMI - body mass index; MV - mechanical ventilation.

* Gastrointestinal, cardio-vascular, metabolic, neurologic, orthopedic/ trauma, renal, pulmonary, sepsis, other. Sepsis was the main admission diagnosis, if there was an infection-associated circulatory dysfunction requiring vasopressor therapy which dominated dysfunction of other organs;

† only used when analyzing the association of daily propofol-associated energy intake (categorized variable) with time-to-discharge alive/in-hospital death (cumulated for the early and late phase after intensive care unit admission);

‡ only used in multistate models

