### Outcome measures

–**Primary outcomes:** time-to-hospital discharge-alive as a surrogate of morbidity, and to in-hospital death (adjusted hazard ratios and 95% confidence intervals [95%CI]).Adjusted hazard ratios compare two levels of daily propofol-associated energy intake. They will be calculated separately for each day after ICU admission using sub-distributional and cause-specific hazard models. The observation period will start on the day of ICU admission, and events (day of discharge alive/in-hospital death) will be registered from day 2 after ICU admission until the end of the lead-time (defined as twice the number of days that a patient received propofol therapy).–**Secondary outcomes:** the risk of state transition (adjusted hazard ratio and 95%CI) and the transition probabilities between the different states (Figure 1).State transition risks and probabilities will be referred to a certain amount of propofol-associated energy intake or a specific duration of propofol therapy; adjusted hazard ratios will be calculated for all 17 transitions (Figure 1). State transition will be registered until day 13 after ICU admission. Initial and absorbing states include "propofol: no/MV: no", "propofol: yes/MV: no", "propofol: no/MV: yes", "propofol: yes/MV: yes", post-transition absorbing states include "in-ICU death" and "ICU discharge alive.

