### Overall design of the multistate models

We will use multistate models to assess the association between cumulated daily propofol-associated energy intake preceding state transition; propofol-associated energy intake on transition day, and number of days with propofol therapy preceding state transition, adjusted for the use of MV, and the subsequent risk for an inevitable state transition (Figure 1).^(21,22)^ We will analyze state transitions on a daily basis (days 0 to 11 after ICU admission), since the database contains information on propofol use and total propofol-associated energy intake on a given day. There are no data on state transitions occurring within 24 hours. Furthermore, transitions between propofol states have only been recorded up to 12 days after ICU admission. This is because propofol data recording stopped if a patient died or was discharged from the ICU, or if they had been in the ICU for more than 11 days. In line with this, for the multistate models, we will only consider outcomes (absorbing states: in-ICU death and discharge from the ICU alive) up to day 12 after ICU admission.

All analyses (multistate models and competing risks, see below) will be performed using the Piecewise Exponential Additive Mixed Model (PAMM). Like the Cox model, this model class is a multiplicative hazards model that estimates the hazard rate (or, more generally, the transition hazards) conditional on the covariates. Coefficient estimates can be interpreted in the same way as in the Cox model, e.g., using hazard ratios. We will use the PAMM rather than the Cox model because it explicitly estimates the baseline hazard and facilitates the estimation of nonlinear and time-varying effects, as well as the inclusion of time-dependent covariates (e.g., the number of previous days on MV). The general idea is to partition the observation period into short time intervals and estimate a constant hazard rate for each interval. This enables the model to capture varying hazard rates at different times after ICU admission, making it suitable for situations where the risk of state transition changes over time (e.g., after ICU admission). In the context of a multistate model, the hazard by piecewise exponential models becomes the transition hazard. Details can be found in the references.^(9,15,23-26)^

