Hazard ratios can be used to describe the association of covariates and exposures with each transition (e.g., from alive to death in the ICU). In multistate settings, separate hazards are estimated for each possible transition. These individual transition hazards are then combined to obtain the overall transition probabilities by calculating the empirical transition matrix. While hazard ratios describe the direct effect on the instantaneous risk of a transition (relative risk), transition probabilities depend on the hazards of all possible transitions (absolute risk). Together, these two quantities provide a comprehensive interpretation of the underlying processes.

A particular focus will be on the concomitant use of MV, which is one of the main reasons for propofol use in critically ill patients and therefore the most important confounder of propofol-associated outcomes. The time-dependent confounder MV is considered as a separate state^(27)^ in the multistate model (Figure 1). This has the advantage that the transitions to the absorbing states "ICU discharge alive" and "in-ICU-death", and thus the transition probabilities to these states, can be modelled separately, depending on the current time-dependent propofol status (yes or no), but also on the subject-specific history of MV treatment and propofol administration (number of days with propofol therapy, cumulated propofol-associated energy intake). As the model is conditional on propofol status at any given time, but the frequency of MV use may vary between subjects within each propofol state, it allows the association of propofol and MV status with outcomes to be disentangled.

Results for the association between the exposure variables preceding transition (number of days with propofol therapy, cumulated propofol-associated energy intake (kcal/kg), propofol-associated energy intake (kcal/kg day) on transition day), and transition risk will be presented as adjusted hazard ratios (with 95%CIs) and adjusted transition probabilities (with 95%CIs) depending on a specific day after ICU admission (Days 1 to 11).

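### The multistate models start on day 0, before the 48-hour entry condition and the days 0–2 nutrition counts are known, so their first two daily steps look ahead

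*Protocol article*

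**What the plan says.** All references are to the protocol article.

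- **Time axis.** Under Overall design of the multistate models: "We will analyze state transitions on a daily basis (days 0 to 11 after ICU admission". The same section says "we will only consider outcomes (absorbing states: in-ICU death and discharge from the ICU alive) up to day 12 after ICU admission". Results are to be presented "depending on a specific day after ICU admission (Days 1 to 11".
- **Entry.** Under Inclusion criteria: "Other inclusion criteria will be an ICU length-of-stay (LOS) of > 48 hours".
- **Covariates.** Table 1 lists "Number of days on oral nutrition", "Number of days on parenteral nutrition" and days with protein intake above 1.2 g/kg, each recorded over "Days 0 - 2 post ICU admission". No footnote keeps these three out of the multistate models. The baseline ventilation count over the same days is restricted by footnote to the competing-risk analysis. The multistate models use ventilation days before the state transition instead.
- **Registration of events.** Outcome measures says of the primary outcomes "The observation period will start on the day of ICU admission", and the same sentence adds that events count only from day 2. For state transitions it gives an end but no delayed start.

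No late entry, left truncation or landmark is stated for the multistate models.

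**The concern.** The entry rule, the time axis and the covariate windows are each fixed in the text, and they do not fit together. Whether a patient belongs to the cohort is known only on day 2, and the three nutrition counts are complete only at the end of day 2. The model nevertheless explains transitions from day 0 onward with them.

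This has two consequences for the first two steps. First, a patient who comes off propofol and ventilation on day 1 can start eating on day 1 or 2, so the oral-nutrition count may be a result of the transition it is meant to adjust for. Secondly, a state change on day 1 is counted only if the patient then stays alive and in the ICU past 48 hours. Patients who were weaned early and left, or who died early, are not there.

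At stake are the early hazard ratios for transitions between propofol and ventilation states, which the multistate model is built to separate, and the transition probabilities that start from day 0 or 1.

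**Working it through.** The plan gives no figure on this point to reproduce. The check sets the stated windows against each other and then illustrates the mechanism.

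**1. Modelled steps.** Starting days 0 to 11, with absorbing states up to day 12, give 12 daily steps.

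**2. Covariate days that lie ahead.** At the step from day x to day x+1, the days of the 0–2 window already seen number min(x, 2) + 1, so 3 − [min(x, 2) + 1] lie ahead.

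| Step | Seen | Ahead |
|---|---|---|
| 0→1 | 1 | 2 |
| 1→2 | 2 | 1 |
| 2→3 and later | 3 | 0 |

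Exactly two steps are affected: 2/12 = 17%. If reported days 1 to 11 are labelled by starting day, one is affected: 1/11 = 9%.

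**3. Exits blocked by the entry rule.** Assume a constant ICU-exit hazard and an admission hour spread evenly over day 0. The documents give neither. In simulation, the daily exit probability among patients still in the ICU was:

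| Calendar day | h = 0.06: all / stay > 48 h | h = 0.10: all / stay > 48 h |
|---|---|---|
| 0 | 0.029 / 0 | 0.049 / 0 |
| 1 | 0.058 / 0 | 0.095 / 0 |
| 2 | 0.058 / 0.029 | 0.095 / 0.048 |
| 3 | 0.058 / 0.058 | 0.095 / 0.095 |

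Exits are fully blocked on days 0 and 1, about half blocked on day 2, and unaffected from day 3. The first clean step is therefore 2→3, for exits as well as for the covariates.

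**4. How a count that looks ahead behaves.** Assume a daily propofol-stop hazard of 0.25 (probability 1 − e^(−0.25) = 0.221), a 50% chance of oral feeding on each day off propofol, and no effect of feeding on stopping.

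- Step 0→1. Among those who stop, the chance of any oral day by day 2 is 1 − 0.5² = 0.75. Among those who do not, it is 0.221 × 0.5 = 0.111. The probability of stopping given any oral day is (0.221 × 0.75) / (0.221 × 0.75 + 0.779 × 0.111) = 0.166 / 0.252 = 0.66. Given none, it is (0.221 × 0.25) / 0.748 = 0.07.
- Step 1→2. Among patients still on propofol on day 1, only those who stop can have an oral day in the window. The probability of stopping is 1.00 given an oral day and 0.111 / 0.889 = 0.12 given none.

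A covariate with no causal effect thus appears strongly related to the transition. The inputs are assumed. The result shows the mechanism and does not estimate bias in a propofol hazard ratio.

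**5. Extent of the selection.** The database holds 21,100 adults, of whom more than 18,000 stayed over 2 days. At most about (21,100 − 18,000) / 21,100 = 14.7% are excluded, all reasons combined.

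**The case against.** Much can be said for the plan, and most of it stands.

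- **Bias from event-free time.** A reader might infer immortal-time bias in the hazard ratios for ICU death and discharge. The documents do not support that. The first 48 hours are free of exits for every patient whatever the exposure, and the piecewise exponential additive model estimates a baseline that varies with time, so it can largely absorb the zero hazard. Under a constant exit hazard h, the forced event-free share of 12-day person-time is 2 / [2 + (1 − e^(−10h))/h], which is 19% at h = 0.03 and 28% at h = 0.15 (assumed values). This measures person-time, not bias.
- **Wrong absolute risks.** A reader might also infer that the early absolute risks are wrong. The target population is defined as patients staying over 48 hours, with a stated reason, and zero early exit is correct for it. What is missing is a statement that probabilities started on day 0 or 1 carry this condition, which nobody can verify on those days.
- **Primary outcomes.** The competing-risk models already register events only from day 2. The point does not reach them.
- **Little information early.** Preceding propofol days can take very few values on the first steps, so those steps say little about duration. This holds for duration, but intake on the transition day varies fully from the start.
- **Loss from a landmark.** Starting later discards early state changes. This is a genuine cost, and it is why an alternative is given.

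None of this answers the covariate problem. A flexible baseline does not repair adjustment for a value observed after the transition. The plan itself uses ventilation days before transition in these models, but does nothing similar for the three nutrition counts.

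**Conclusion.** The plan contains a look-ahead error in a stated secondary analysis. On 2 of 12 modelled steps, three covariates include days on or after the transition, and state changes are selected on later survival and ICU stay. The affected results are the early hazard ratios for transitions between propofol and ventilation states, and transition probabilities started before 48 hours.

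The count of affected steps follows from the text alone. It assumes only that Table 1 applies to the multistate models as written. The size of the bias in any propofol hazard ratio cannot be derived from the documents, nor can the share of all state changes that falls on these steps. The point is worth correcting because the remedy needs only data already collected. It does not put the primary analysis in doubt.

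**What to change.** **Preferred.** Let patients enter the multistate risk set with their state on day 2, so that the first modelled step is day 2 to day 3. Use days 0–1 only to build the history of propofol days, cumulated intake and ventilation days. Report transition probabilities conditional on being in the ICU at that landmark. Starting with this step also avoids the partly blocked exits on day 2. Simply equating 48 hours with the start of day 2 would not, because day 0 is a partial day and the data are daily.

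**Alternative, if the early steps are to be kept.** Replace the three days 0–2 counts by running counts up to the day before transition, in the way Table 1 already handles ventilation. State that early transition probabilities are conditional on an ICU stay over 48 hours.

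**Cost.** Both options need recoding of existing data and a few sentences. With the landmark, state changes on days 0–1 are described but not modelled, and exits on day 2 are not used. The alternative keeps those steps, but they remain selected on later ICU stay.

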### Research question

The average causal effect of propofol on the risk of in-hospital all-cause death has been demonstrated in previous clinical trials. Associations between propofol doses, timing, and responses, however, are unknown. The present study aims to fill this gap. The primary research question focuses on the association between defined levels of propofol-associated energy intake in the early and late phases following ICU admission and competing risks (time to discharge alive (being a surrogate of morbidity), and in-hospital death, respectively). The secondary research question centers on the association between preceding cumulated or daily propofol energy intake, or the number of days on propofol prior to transitioning from propofol to, e.g., death or being free of propofol the day after transitioning. These factors will be examined in terms of measured variables and transition probabilities, while accounting for bias from confounding by indication or palliative care. The general aim is to provide more evidence on safe propofol dosing and duration.

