## METHODS

### Data base

The International Nutrition Survey is a multinational database of critically ill adults treated in 785 international medical, surgical, or trauma ICUs. This database includes, in addition to nutritional and outcome data, information on daily propofol use and associated fatty acid intake and has collected data on more than 20,000 critically ill patients. Details of this database have been presented in a previous publication, and to date, the results of 18 previous studies have been based on various subgroups included in this database. Details of these studies, which addressed various aspects related to medical nutrition therapy, can be found in the electronic database.^(9)^

The core of the present study will be the analysis of a subpopulation of this multinational database. Patients enrolled in this database were followed from the day of ICU admission. Nutritional and clinical parameters (including daily protein intake, lipid intake, use of MV, propofol, and propofol-associated fat energy intake (including soybean oil and purified egg phosphatide) were collected daily from Day 0 (day of ICU admission) until ICU discharge or death, or for a maximum of 12 days for patients still in the ICU. Survival was assessed until hospital discharge (dead or alive) up to 60 days from ICU admission. Only ICUs with at least one included patient were kept in the database.

During the ICU stay, patients received standard medical care (including MV and propofol) at the treating physician's clinical judgement. The principles of sedation, ventilation strategies, including lung protective ventilation, weaning, and prevention/therapy of ventilator-associated pneumonia, followed international guidelines in effect at the time of the data collection.^(10-13)^

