#### Data collection

Using a secure web-based data collection tool, the following information was collected: date of ICU admission, admission category (elective surgery, emergency surgery, and medical), primary admission diagnosis (nine categories), sex, age, BMI, daily use of MV/propofol therapy, and Apache II score on the day of admission. Attending physicians or allied healthcare professionals with expertise in nutrition practices (e.g., dietitians) also recorded daily protein intake and route of additional caloric intake (enteral nutrition, parenteral nutrition). For the first 11 days after ICU admission, the database contains information on protein and energy intake, as well as the number of days on which a patient received parenteral nutrition or oral feeding at any time.

Daily propofol-associated energy intake was also collected from the day of ICU admission (partial day) to a maximum of 11 additional days after admission. Information on the exact dose of propofol (administered via 1% or 2% solutions) was not available in the database. However, as propofol-associated energy intake is closely related to the dose of propofol, propofol-associated energy intake can be used as a surrogate parameter for this dose (1mL of a solution containing propofol contains 50mg of soybean oil, and 50mg of purified egg phosphatide, equivalent to 1.1kcal/mL).

Patients were followed in the hospital for a maximum of 60 days after ICU admission. We recorded the time to in-hospital death or discharge alive. Patients who remained alive in the hospital for more than 60 days were considered censored for both risks at that time.

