### Sensitivity analysis for the multistate models

If it is decided to withdraw established life-sustaining therapies (e.g., MV) based on the presumed wishes of the patient (e.g., communicated by a surrogate) or the instructions of an advance directive, sedation may be changed to drugs stronger than propofol (midazolam), and opioids (morphine, etc.) are added to analgo-sedate the patient. Death usually occurs one to two days after these therapeutic changes. Consequently, in these cases, the transition from propofol to no propofol would not indicate an improvement in clinical status (as it would otherwise). To account for this bias within the transition from the state "propofol: yes" to the state "propofol: no", we will re-classify the subsequent absorbing state "in-ICU death" into "palliative in-ICU death", if death occurs one or two days after the preceding state transition (time course of states # 1 - 7, Table 3), and into "non-palliative death" in all other time courses of states.

**Table 3 t3:** Survey of time courses of different daily states used to re-define the absorbing state "in-intensive care unit death" into "palliative in-intensive care unit death" (time course of states #1 to #9) and "non-palliative in-intensive care unit death" (all other time courses)

Time course of states #	State on day x minus n (n > 2)	State on day x minus 2	State on day x minus 1	Initial state (day x)	Absorbing state (day x plus 1)
1	Any	Any	"Propofol: yes" "MV: yes"	"Propofol: no" "MV: yes"	In-ICU death
2	Any	Any	"Propofol: yes" "MV: no"	"Propofol: no" "MV: no"	In-ICU death
3	Any	Any	"Propofol: yes" "MV: yes"	"Propofol: no" "MV: no"	In-ICU death
4	Any	"Propofol: yes" "MV: yes"	"Propofol: no" "MV: yes"	"Propofol: no" "MV: yes"	In-ICU death
5	Any	"Propofol: yes" "MV: no"	"Propofol: no" "MV: no"	"Propofol: no" "MV: no"	In-ICU death
6	Any	"Propofol: yes" "MV: yes"	"Propofol: no" "MV: yes"	"Propofol: no" "MV: no"	In-ICU death
7	Any	"Propofol: yes" "MV: yes"	"Propofol: no" "MV: no"	"Propofol: no" "MV: no"	In-ICU death
8	Any	Any	"Propofol: no" "MV: no"	"Propofol: yes" "MV: no"	In-ICU death
9	Any	"Propofol: no" "MV: no"	"Propofol: yes" "MV: no"	"Propofol: yes" "MV: no"	In-ICU death

MV - mechanical ventilation; ICU - intensive care unit.

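### The multistate palliative-care sensitivity analyses re-define only in-ICU death, so end-of-life transfers followed by death on a ward stay in ICU discharge alive

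*Protocol article*

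**What the plan says.** Under *Overall design of the multistate models*, the protocol article fixes the end states and the horizon: "we will only consider outcomes (absorbing states: in-ICU death and discharge from the ICU alive) up to day 12 after ICU admission". The reason given for the short horizon concerns exposure: "This is because propofol data recording stopped if a patient died or was discharged from the ICU", or once the stay went beyond day 11.

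Follow-up for death is longer. *Data base* says "Survival was assessed until hospital discharge (dead or alive) up to 60 days from ICU admission", and *Data collection* says "We recorded the time to in-hospital death or discharge alive".

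The *Research question* section sets the secondary question "while accounting for bias from confounding by indication or palliative care". For the multistate models this is done in *Sensitivity analysis for the multistate models*: "we will re-classify the subsequent absorbing state 'in-ICU death' into 'palliative in-ICU death", when death follows a propofol change by one or two days (Table 3, time courses 1 to 9). For the two intake-based exposures, Table 2 uses an intake rule instead: a rise of at least 100% from the day before, or more than 4.5 kcal/kg on the transition day. All three rules apply to in-ICU death only.

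The primary outcomes are measured at hospital level: "time-to-hospital discharge-alive as a surrogate of morbidity, and to in-hospital death".

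**The concern.** The protocol's own argument is that stopping propofol when life-sustaining therapy is withdrawn is not a sign of improvement, and that death then usually follows within one to two days. The argument does not depend on where the patient dies. The correction does. If the patient dies before leaving the ICU, the death is set apart as palliative. If the patient is moved to a ward first, the same decision ends in ICU discharge alive, and no multistate analysis looks at it again.

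At stake is how the discharge transitions are read. Their hazard ratios and transition probabilities, the latter described as absolute risks, are meant to support statements on safe propofol dosing and duration. If end-of-life transfers form a noticeable part of the discharges from a given state, the association of propofol with leaving the ICU alive mixes recovery with dying. The planned sensitivity analyses would not show this.

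**Working it through.** **Step 1. Is the later death known?** Yes. Time to in-hospital death is recorded up to day 60. The end of propofol recording at ICU discharge explains why exposure and the transient states stop there. It does not explain why a recorded death shortly afterwards is not used to label the end state in a sensitivity analysis.

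**Step 2. Follow two patients through Table 3.** Both receive propofol and ventilation on day x − 1 and neither on day x.

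- Patient A dies in the ICU on day x + 1. This is time course 3, so the death is re-defined as palliative in-ICU death.
- Patient B goes to a ward on day x + 1 and dies there on day x + 1 or x + 2, one or two days after the same change. No rule in Table 2 or Table 3 applies, so B stays in ICU discharge alive.

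The route is plausible within the table itself. In five of the nine time courses (2, 3, 5, 6 and 7) the patient is off both propofol and ventilation on the last day before death.

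**Step 3. How many patients could be involved?** From *Sample size considerations*: more than 18,000 patients and about 70% discharged alive by day 60.

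- Plan's figure: 18,000 × 0.70 = 12,600, which agrees with the stated more than 10,000 discharges.
- Remainder: 18,000 − 12,600 = 5,400 who died in hospital or were still there at day 60. The document does not divide them by place of death.
- Assumption (not in the document): a share s of the 5,400 left the ICU alive by day 12 and later died in hospital. Then s = 5% gives 5,400 × 0.05 = 270, s = 20% gives 1,080, and s = 40% gives 2,160.

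These counts include all later hospital deaths, some of them weeks after discharge. Only those within one or two days of a propofol change belong to the palliative question, and nothing in the document sizes that part.

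**Step 4. What could mixing do to a hazard ratio?** The discharge hazard is the sum of two hazards: discharge followed by survival to hospital discharge, and discharge followed by in-hospital death. With f the second type's share of the discharge hazard in the reference group,

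pooled HR = (1 − f) × HR for the first type + f × HR for the second type.

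Take an assumed HR of 0.90 for the first type:

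| f | second-type HR 1.0 | second-type HR 1.5 | second-type HR 2.0 |
|---|---|---|---|
| 2% | 0.902 | 0.912 | 0.922 |
| 5% | 0.905 | 0.930 | 0.955 |
| 10% | 0.910 | 0.960 | 1.010 |
| 15% | 0.915 | 0.990 | 1.065 |

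For example, 0.90 × 0.90 + 0.10 × 1.5 = 0.81 + 0.15 = 0.96. All inputs to this table are assumed. At f = 2% the effect is slight. It becomes material only if f is near 10% and the second-type hazard ratio is well above 1.

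**The case against.** The strongest reply is that nothing is coded wrongly. ICU discharge alive means that the patient left the ICU alive, which is true of patient B. The protocol never calls this state favourable, reports each transition separately, and does not offer in-ICU death as total mortality. The endpoint is secondary, and the primary analysis uses hospital discharge alive and in-hospital death, so ward deaths count as deaths there within the lead-time window (twice the number of propofol days). That analysis also has a two-day lag sensitivity analysis and reports absolute risk through cumulative incidence functions. Ending the multistate models at ICU discharge is a coherent ICU-level question.

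All of this stands and limits the weight of the point. A reader might infer that the plan counts dying patients as successes, that it understates in-ICU death, or that ICUs which transfer dying patients will look better. The document does not support these readings. The states are measured as labelled, no comparison of ICUs is planned, and every model has a random effect for the unit, which may absorb part of the difference in transfer practice.

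What the reply does not answer is the gap in the sensitivity analysis. The protocol undertakes to account for palliative-care bias in the multistate models and builds a rule on the timing of propofol changes, then applies it to one of the two end states. The primary analysis does not fill the gap, because it does not give the transition-specific results by days on propofol or cumulated intake, with ventilation as a state.

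**Conclusion.** The point holds in a limited form. The palliative-bias correction in the secondary multistate models is incomplete for the transitions to ICU discharge alive, although the death times needed to complete it are recorded. It is not an error in the state definitions, and it does not touch the primary analysis.

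The size is unknown. The 270 to 2,160 range rests on an assumed share and counts all later hospital deaths, so it is no estimate of the palliative group. The hazard-ratio table is an illustration with assumed inputs. Figures 1 and 2 are not available here; the conclusion rests on the text and on Tables 2 and 3, which name only in-ICU death for re-definition. This is a worthwhile, inexpensive improvement to an analysis already planned.

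**What to change.** In the existing multistate palliative-care sensitivity analysis:

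1. Split ICU discharge alive into discharge followed by in-hospital death and all other discharges.
2. Class a discharge with palliative death only when a propofol/ventilation time course of the Table 3 type precedes it and death falls within the protocol's one-to-two-day window, counted from that change. Keep other post-ICU deaths as a separate, non-palliative category. Labelling every ward death soon after discharge as palliative would depart from Table 3, which requires a preceding propofol change, and would sweep in unexpected ward deaths.
3. Report the number of later in-hospital deaths among ICU discharges, by initial state.
4. State that ICU discharge alive is not to be read as recovery.

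The cost is a derived state from dates already held and an extension of a planned run. No exposure definition or primary analysis changes. There are two small drawbacks: the split uses information from after ICU discharge, and the added state may have few events for some transitions. Where it does, the counts in item 3 can be reported without a model.
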